### Trial design {8}

A two-armed, parallel-design RCT will occur where participants receive the 10-week app-based BEAM program (mental health and parenting treatment) or MoodMission (mental health treatment only). Mothers will be randomized to the BEAM or MoodMission program with a 1:1 allocation as per a computer-generated randomization schedule stratified by participant availability for weekly group telehealth sessions. Self-reported repeated measures data will be collected online via Research Electronic Data Capture (REDCap) [31] from mothers in both programs. Back-end BEAM App data will be collected via Google Analytics and Firebase. Assessments will occur at three timepoints: pre-intervention (T1), post-intervention (T2), and 6-month follow-up (T3). Amendments to the study protocol will be submitted to the Research Ethics Board (REB) at the University of Manitoba who will review and approve amendments prior to implementation. Participants will re-consent to amendments, if required. Any amendments will also be submitted as updates on ClinicalTrials.gov.

This trial is registered with ClinicalTrials.gov (NCT05398107) and will follow Standard Protocol Items: Recommendations for Intervention Trials (SPIRIT) guidelines [32, 33]. All procedures will be performed in accordance with the University of Manitoba’s REB (HE2021-0217) and the Helsinki Declaration. Participants will provide electronic informed consent prior to study enrollment.

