##### Pre-intervention questionnaires

All mothers deemed eligible to participate will be invited to complete a series of questionnaires via RedCap to assess baseline data of interest before allocation. See Table 2 for specific questionnaires.

**Table 2 Tab2:** Schedule for assessment administration

Study period					
**TIMEPOINT**	**Enrolment**	**Allocation**	**Intervention**	**Post-intervention**	**Follow-up**
	***Weeks 1–8***	**Week 9**	***Weeks 9–19***^v^	***Weeks 19–21***	***Weeks 32–34***
**Adverse Childhood Experiences**^**a**^	X				
**Ages and Stages Questionnaire: Social-Emotional, Second Edition** *(6, 12, 18, 24, 30, 36 months)*^b^	X			X	X
**Alcohol Use Disorder Identification Test**^**c**^	X			X	X
**Anxiety Persistence Scale**^a^				X	
**BEAM**^d^** App-Based Questionnaire**^a^				X	
**BEAM**^d^** Forum Questionnaire**^a^				X	
**BEAM**^d^** Perceived Social Support Questionnaire**^a^				X	
**BEAM**^d^** Zoom Telehealth Group Questionnaire**^a^				X	
**Cannabis, Tobacco, and Illicit Drug Use**^a^	X			X	X
**Cannabis Use Disorder Identification Test – Revised**^e^	X			X	X
**Couples Satisfaction Index – 4 Item**^f^	X			X	X
**Depression Persistence Scale**^a^	X				
**Depressive Symptom Index – Suicidality Subscale**^g^				X	X
**Emergency Health & Social Service Utilization**^a^	X			X	X
**Generalized Anxiety Disorder – 2 Item**^h^			X		
**Generalized Anxiety Disorder – 7 Item**^i^	X			X	X
**Infant Behavior Questionnaire – Very Short – Revised**^j^	X			X	X
**mHealth App Usability Questionnaire**^k^				X	
**Mini International Neuropsychiatric Interview**^l^	X				
**Mood Mission App-Based Questionnaire**				X	
**Parenting Scale** *(modified 10 item scale)*^m^				X	X
**Parenting Stress Index**^n^	X			X	X
**Parenting Stress Index** *(modified 4 item scale)*^a^			X		
**Patient Health Questionnaire – 2 Item**^o^			X		
**Patient Health Questionnaire – 9 Item**^p^	X			X	X
**Patient-Reported Outcomes Measurement Information System** *(Anger and Sleep Disturbance Subscales)*^q^	X			X	X
**Pediatric Quality of Life Inventory** *(1–12 or 13–24 months)*^r,s^	X			X	X
**Perceived Maternal Parenting Self-Efficacy Questionnaire**^t^	X			X	X
**Positive and Negative Affect Scale** *(modified 2-item scale)*^u^			X		
**Recent Stressful Experiences**^a^	X			X	X
**Sociodemographics**^a^	X				
**Substance Use Motives Measure** *(Coping Motive Subscales)*^v^	X			X	X

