***Aim 2***		
Treatment response	Comparison between groups	Significant group difference in primary clinical outcomes (depression and anxiety)
Treatment effect	Estimate of effect size and variance for future sample size calculations	Data on all relevant variables
Baseline severity moderation	Comparison of those with low versus high baseline scores on the PHQ-9 and GAD-7	Significant group difference

#### Aim 1

Back-end App data, collected via Google Analytics and Firebase, will be used to assess recommended mHealth engagement variables [46, 47]: (a) number of logins and sessions to the BEAM app, (b) number of forum posts, (c) time spent on the BEAM app and on the forum, (d) number of videos watched/time spent watching videos, and (e) number of weeks between first and last engagement with the app. Weekly telehealth group session attendance (yes/no) will be compiled by the clinical team. Analytics and group attendance data will also be used to assess retention (number of weeks completed) and completion (participating in > 50% of program weeks by either logging onto the BEAM app or attending the weekly group telehealth session). Finally, the mHealth App Usability Questionnaire (MAUQ) [48] will assess participants’ views on the BEAM program.

#### Aim 2

Data on maternal depression (PHQ-9) and anxiety (GAD-7) will be used to estimate effect size for a future large-scale RCT and to assess preliminary mean change in variables of interest across assessment timepoints. The PHQ-9 includes [35] nine items which will ask mothers the severity of their depressive symptoms during the past 2 weeks. The PHQ-9 has high internal consistency (*α* = 0.88) [49]. Anxiety symptom severity will be assessed using the GAD-7, a seven-item measure which will ask mothers their degree of anxiety symptoms over the past 2 weeks. The GAD-7 has excellent internal consistency (*α* = 0.92) [36]. Items on both scales are scored on a 4-point Likert scale ranging from 0 (“Not at all”) to 3 (“Nearly every day”) where higher summative scores suggest more problematic symptoms.

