### Statistical methods {20a}

All analyses will be conducted using IBM Statistical Package for the Social Sciences (SPSS). Descriptive statistics will be computed for the total sample and between the two groups (i.e., BEAM and MoodMission) for demographics and outcome measures at pre-intervention.

#### Aim 1

Descriptive statistics from back-end App data, telehealth group attendance, and questionnaires (i.e., BEAM App-Based, BEAM Forum, BEAM Perceived Social Support, BEAM Zoom Telehealth Group, mHealth App Usability, and MoodMission App-Based) will be used to examine program feasibility, engagement, and acceptability.

#### Aim 2

Data on maternal depression (PHQ-9) [35] and anxiety (GAD-7) [36] will be used to estimate effect size and variance for future sample size calculations. Preliminary analyses will also examine treatment effects on outcomes of interest (e.g., depression, anxiety). A longitudinal analysis of covariance, using linear mixed modelling, will be conducted to preliminarily test treatment effects on outcomes of interest. Treatment effects will be tested using two-way interactions between time and group assignment. Baseline moderation by symptom severity will be assessed to determine whether the BEAM program helps reduce symptoms for mothers with higher levels of depression and anxiety at pre-intervention compared to MoodMission. An *α* of 0.05 will determine statistical significance. Aggregate variables will be computed, by converting each measure to a standardized *z*-score then taking the average. Results will be reported as means and 95% confidence intervals for all comparisons. Bonferroni corrections are considered very conservative [64], and it has been suggested that correction may not be necessary, particularly if the study purpose is exploratory [65].

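### The protocol pairs a longitudinal ANCOVA with a time-by-group test without saying whether T1 is covariate or outcome; under the usual reading that test misses a sustained benefit

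*Protocol article*

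**What the plan says.** Statistical methods {20a}, Aim 2, names the model: "A longitudinal analysis of covariance, using linear mixed modelling, will be conducted to preliminarily test treatment effects on outcomes of interest". The next sentence names the test: "Treatment effects will be tested using two-way interactions between time and group assignment". The section sets the level ("0.05 will determine statistical significance") and promises means with 95% confidence intervals for all comparisons. It does not name a group effect or a visit-specific contrast as the test, and it does not place T1 in the model. Additional analyses {20b} reuses the same longitudinal analysis of covariance by reference.

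Trial design {8} sets three assessments: pre-intervention (T1), post-intervention (T2) and 6-month follow-up (T3). Outcomes {12}, Aim 2, says the PHQ-9 and GAD-7 data will be used, among other things, "to assess preliminary mean change in variables of interest across assessment timepoints". Table 3 defines treatment response as a between-group comparison whose success criterion is a significant group difference in depression and anxiety. The text above that table says every indicator is classed as success or revise.

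Table 2 schedules the Parenting Scale ("modified 10 item scale") and the "Depressive Symptom Index – Suicidality Subscale" (DSI-SS) at post-intervention and follow-up only. Outcomes {12} lists both among the additional questionnaires.

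**The concern.** The named model and the named test fit together only under some parameterisations, and the protocol does not say which applies.

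In a longitudinal ANCOVA as usually understood, T1 is a covariate and T2 and T3 are the outcomes. The treatment effect is the baseline-adjusted difference between arms. With conventional coding (group, time and their product), the time-by-group term asks whether that difference changes between T2 and T3. A program that works by week 10 and holds its gain makes this term zero.

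If T1 is one of three repeated outcomes, time-by-group does measure differential change from baseline, but the model is no longer an ANCOVA in the usual sense. Unless the arms are given a common baseline mean, the contrast is a difference in change scores and does not adjust for baseline.

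The two readings can give opposite verdicts on the same data. At stake are the treatment-response row of Table 3 and the choice of effect estimate to carry into the future trial's sample size, which is the stated purpose of Aim 2.

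**Working it through.** **The plan's own figures.** The protocol gives no power for this comparison, so there is none to reproduce. Its only precision figures concern feasibility, at 40 mothers: 1.96 × √(0.8 × 0.2/40) = 12.4% and 1.96 × √(0.5 × 0.5/40) = 15.5%. Both match Sample size {14} but do not bear on this test.

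**Inputs from the protocol.** 1:1 allocation; 40 per arm recruited; 30% attrition, so 40 × 0.7 = 28 per arm (the stated target is 30); α = 0.05, taken as two-sided.

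**Assumed inputs, because the protocol gives none.** SD 1 at each visit; true effect d = 0.5 at both T2 and T3; complete data at n per arm. Write r1 for the correlation of T1 with T2 and with T3, and r2 for that of T2 with T3. Three sets (r1, r2) are used: (0.4, 0.6), (0.5, 0.5), (0.6, 0.7).

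**Formulas.** For a single contrast, z = effect / √((2/n) × V) and power = Φ(z − 1.96) + Φ(−z − 1.96).

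- ANCOVA time-by-group (T3 effect minus T2 effect): V = 2(1 − r2), effect = d − d = 0.
- Adjusted T2 difference: V = 1 − r1².
- Adjusted mean of T2 and T3: V = (1 + r2)/2 − r1².
- T1 as an unconstrained third outcome, 2-df interaction: each change from T1 has variance 2(1 − r1), and the two changes have covariance 1 + r2 − 2r1. With equal effects the noncentrality is λ = d² × (n/2) × 2 / [2(1 − r1) + 1 + r2 − 2r1]. Power is the chance that a noncentral chi-square on 2 df exceeds 5.991.

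**Worked case, n = 28, set (0.4, 0.6).**

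- Adjusted T2: V = 0.84, z = 0.5/√(0.0714 × 0.84) = 2.04, power 53%.
- Adjusted mean: V = 0.80 − 0.16 = 0.64, z = 2.34, power 65%.
- Unconstrained 2-df: λ = 0.25 × 14 × 2/(1.2 + 0.8) = 3.5, power 37%.
- ANCOVA interaction: z = 0, rejection 5%.

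**All three sets, d = 0.5 sustained.**

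| Test | n = 28 per arm | n = 30 per arm |
|---|---|---|
| ANCOVA time-by-group | 5%, 5%, 5% | 5%, 5%, 5% |
| Unconstrained three-visit interaction, 2 df | 37%, 48%, 54% | 39%, 50%, 57% |
| Adjusted T2 difference | 53%, 58%, 65% | 56%, 61%, 68% |
| Adjusted mean of T2 and T3 | 65%, 75%, 76% | 68%, 78%, 79% |

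**Simulation check.** In 600 simulated trials at 30 per arm, d = 0.5 and all correlations 0.5, the ANCOVA interaction rejected in 4.8%, the T2 effect in 62%, the averaged group effect in 80%, and the unconstrained three-visit interaction in 51%.

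**What the 5% depends on.** It does not depend on n, on the correlations, or on the size of the sustained effect. It does depend on the effect being equal at T2 and T3. At 30 per arm and r2 = 0.5, V = 1 and the standard error is √(2/30) = 0.258. An effect falling from 0.5 to 0.25 gives z = 0.97 and 16% rejection; one falling from 0.8 to 0 gives z = 3.10 and 87%. Under this reading the test therefore favours a benefit that disappears over one that lasts.

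**Outcomes without T1.** For the Parenting Scale and DSI-SS only T2 and T3 exist, so on Table 2's schedule a conventionally coded time-by-group term can only be T2-to-T3 change, wherever T1 sits for the other measures.

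**The case against.** The strongest reply is that the protocol never makes T1 the covariate. Three timepoints and the stated interest in mean change across them also fit a mixed model with T1 among the outcomes, where time-by-group interactions are the treatment effect. This stands. A reader might infer that the planned test is simply powerless; the document does not support that, because the 5% result needs T1 as covariate, conventional coding and an equal effect at both visits.

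A reader might also infer that putting T1 in the outcome vector necessarily loses baseline adjustment. That is wrong. If the arms share a common T1 mean and there is no group main effect, the T2 and T3 interactions are the baseline-adjusted differences and have essentially the power of the adjusted contrasts above. Likewise, with T1 as covariate but no group main effect in the coding, the plural interactions would be visit-specific adjusted differences. The protocol neither states nor excludes these codings.

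Two further replies carry part of the weight. Table 3 speaks of a group difference, and intervals are promised for all comparisons, so the interaction sentence may be loose shorthand; but it is the only sentence that says how treatment effects are tested. Parameterisation is often left to an analysis plan, which is not shown here. Its absence is not the point: the protocol has itself fixed a model and a test that do not match as normally understood.

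On size, 28 complete cases per arm is somewhat pessimistic, given the target of 30 and the planned full information maximum likelihood. The n = 30 column shows that this changes little. The Parenting Scale and DSI-SS are additional questionnaires; PHQ-9 and GAD-7 do have T1 scores. The section on discontinuing interventions {11b} mentions suicidality alerts from the pre-intervention survey, but the PHQ-9 item alone could produce these, so they do not establish a T1 DSI-SS.

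**Conclusion.** The point holds as an ambiguity with real consequences. Under the usual meaning of the named model, the stated test rejects in 5% of trials when the benefit is sustained, so treatment response would be classed as revise about 95% of the time for each outcome. Under an unconstrained three-visit model the test is valid but not baseline-adjusted, with about 37–54% power against 53–65% for the adjusted T2 difference and 65–76% for the adjusted T2/T3 mean (28 per arm). Those ranges rest on the assumed d = 0.5, unit SD and the three correlation sets; the 5% rests on the reading and on an equal effect at T2 and T3. Under a common-baseline model the stated test would be sound.

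Severity is moderate. Aim 2 is labelled preliminary, no power is claimed, the registered primary outcomes are feasibility measures, and treatment response is one of twelve rows in Table 3. The issue with the Parenting Scale and DSI-SS is correct on Table 2 but secondary.

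**What to change.** Replace the interaction sentence in Statistical methods {20a} with a statement along these lines:

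- The T2 and T3 scores are the outcomes, the T1 score is a covariate and time is categorical. Equivalently, T1 is in the outcome vector of a mixed model with a mean common to both arms.
- The treatment effect is the baseline-adjusted BEAM minus MoodMission difference at T2 and at T3, each reported with its 95% confidence interval.
- One of the two, named before analysis, decides treatment response in Table 3.
- The T3-minus-T2 contrast is reported only to describe durability.

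For the Parenting Scale and DSI-SS, state that the arms are compared directly at T2 and T3 and not through the interaction. Whether to adjust those comparisons for a related T1 score already collected is the investigators' choice.

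The cost is wording in the protocol or analysis plan. No new data, visits or participants are needed, and the model remains a linear mixed model that can be fitted in the planned software.

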### Additional analyses {20b}

A separate subgroup analysis will be conducted with mothers who report at-risk substance use. This analysis will assess outcomes among mothers with at-risk substance use in the BEAM program and MoodMission. Between- and within-group differences will be examined among mothers with at-risk substance use (an 8 + on the AUDIT and/or CUDIT-R^52^,^53^) and non-problematic substance use (< 8 on the AUDIT/CUDIT-R^52^,^53^). An examination of demographics on feasibility data and a longitudinal analysis of covariance (as described above) will also be conducted.

### Definition of analysis population related to protocol non-adherence and methods to handle missing data {20c}

An intent-to-treat analysis will be conducted where missing data will be handled using full information maximum likelihood estimation [66]. Sensitivity analyses will be conducted by re-running analyses with completers only [67].

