*Note*. ^a^Author-Compiled Questionnaire; ^b^Squires et al. (2015)^c^Babor et al. (2001)^d^BEAM = Building Emotional Awareness and Mental health^e^Adamson & Sellman (2003)^f^Funk & Rogge (2007) ^g^Stanley et al. (2021)^h^Kroenke et al. (2007)^I^Spitzer et al. (2006) ^j^IBQ-VS-R (Putnam et al., 2014) ^k^Zhou et al. (2019) ^l^Sheehan et al. (1998) ^m^Irvine et al. 1999 ^n^Barroso et al. (2016) ^o^Kroenke et al. (2003) ^p^Kroenke et al. (2001) ^q^PROMIS (Hanish et al., 2017; Pilkonis et al., 2011) ^r^Physical Functioning, Physical Symptoms, Emotional Functioning, Social Functioning, and Cognitive Functioning Subscales ^s^Varni et al. (1999) ^t^Barnes & Adamson-Macedo (2007) ^u^Watson et al. (1988) ^v^Biolcati & Passini (2019); ^v^Weekly questionnaires are only administered to those in the BEAM program

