##### MoodMission (Standard of Care Group)

The SOC arm will receive MoodMission, an App-based program effective in the treatment of moderate depression and anxiety in adults and increasing their well-being [27–30]. MoodMission uses an adaptive learning algorithm based on self-reported level of distress during prior engagement. Based on this algorithm, participants are provided with five targeted cognitive-behavioral therapy strategies to build self-efficacy. Compared to BEAM, this self-paced generalized service is not tailored to the complex needs faced by parents and lacks coaching, social support, and parenting skills development. MoodMission was chosen as the SOC because it has been rigorously studied using RCTs [27–30]. Those in the MoodMission group will work through program content on the App at their own pace.

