***Aim 1***		
Recruitment rate	Number of mothers per week recruited	Mean 2 participants/week
Retention rate	% of mothers with data at follow-up	> 80% of mothers with follow-up data
Perceived usefulness	Usefulness subscale of mHealth App Usability Questionnaire	Mean score of < 3
Processing time	Time from initial contact until study enrollment	Mean time is < 1 week
Post-intervention questionnaire completion time	Time to complete post-intervention questionnaires	Mean of < 60 min to complete
Follow-Up questionnaire completion time	Time to complete follow-up questionnaires	Mean of < 60 min to complete
Questionnaire completion	% of missing data among program completers	> 80% of data is present among mothers who completed follow-up
Treatment adherence	Logging onto BEAM App and/or attending weekly group telehealth session	Participation in > 50% of program weeks via logging onto BEAM App or attending weekly group telehealth session
Safety	Adverse events from the BEAM program or assessments	No adverse events reported

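### The questionnaire-completion indicator has conflicting denominators, and the completers-only sensitivity analysis rests on a term that is undefined and, where defined elsewhere, applies to BEAM alone

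*Protocol article*

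**What the plan says.** Outcomes {12} dichotomises every feasibility indicator into success or revise. In the questionnaire-completion row of Table 3, the indicator is the percentage "of missing data among program completers" and the criterion is "> 80% of data is present among mothers who completed follow-up". A separate row sets retention at more than 80% of mothers with follow-up data. Sample size {14} quotes a precision of ±12.4% around 80% for both questionnaire completion and retention, from an estimated 40 BEAM mothers.

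Section {20c} plans an intent-to-treat analysis with full information maximum likelihood and then adds: "Sensitivity analyses will be conducted by re-running analyses with completers only". It does not say who is a completer. Outcomes {12}, under Aim 1, gives the only rule in the document: "completion (participating in > 50% of program weeks by either logging onto the BEAM app or attending the weekly group telehealth session". The treatment-adherence criterion in Table 3 repeats it.

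For the control arm, the MoodMission section says "Those in the MoodMission group will work through program content on the App at their own pace". Trial design {8} says "Back-end BEAM App data will be collected via Google Analytics and Firebase" and names no such source for MoodMission. The note to Table 2 adds "Weekly questionnaires are only administered to those in the BEAM program".

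**The concern.** The two halves of the Table 3 row would be complements (share missing, share present) only if they referred to the same mothers, and they do not. A mother can attend most BEAM weeks and skip the follow-up survey, or answer the survey after dropping out of the program. Whether the trial reads success or revise can therefore depend on a choice the plan leaves open, while the precision statement assumes a third set.

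The completers-only re-run is the only sensitivity analysis named for missing data. If it follows the program rule, no MoodMission mother can qualify as the rule is written, so it cannot be a like-for-like comparison of the randomised arms. If it means mothers with outcome data, it can be applied in both arms but leaves the main assumption of the likelihood analysis untested. Aim 2 exists to supply effect sizes for a later trial, so a re-run that leans towards BEAM, or that appears to confirm the main result without testing it, could mislead that planning.

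**Working it through.** **Step 1. Reproduce the plan's precision.** The half-width is 1.96 × √(p(1 − p)/n). With n = 40:
- p = 0.80: 1.96 × √(0.16/40) = 12.4%, as stated.
- p = 0.50: 1.96 × √(0.25/40) = 15.5%, as stated for adherence.

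The plan's figures are arithmetically right for all 40 BEAM mothers.

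**Step 2. Same formula, Table 3 denominators, p = 0.80.** Table 3 does not say whether MoodMission mothers count. I follow Sample size {14} and take BEAM alone.

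| Denominator | n | Half-width |
|---|---|---|
| All BEAM mothers | 40 | ±12.4% |
| Completed follow-up, 80% retained | 32 | ±13.9% |
| Completed follow-up, the plan's 30% attrition | 28 | ±14.8% |
| Program completers, if 50% of BEAM (assumed) | 20 | ±17.5% |

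**Step 3. Can the denominator change the verdict?** Take 83.7% retention, which the protocol reports for a recent BEAM iteration, and assume that responders fill in 95% of items.
- Retention: 83.7% > 80%, success.
- Data present among follow-up responders: 95%, success.
- Data present among all BEAM mothers: 0.837 × 0.95 = 79.5%, revise.
- Data present among program completers, if they too answer at 83.7%: 79.5%, revise. In general this reading fails when their response rate is below 0.80/0.95 = 84.2%.

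**Step 4. What both T3 thresholds together allow.** At the two limits, the follow-up data present among all randomised mothers are 0.80 × 0.80 = 64%. For T2, Table 3 has a completion-time row but no response-rate row.

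**Step 5. Size of a one-arm filter.** This is conditional on a reading that section {20c} does not state. Assume no true effect, a proportion p of 40 BEAM mothers kept, all 40 controls kept, and correlation r between participation and outcome. With c = Φ⁻¹(1 − p) and m = φ(c)/p, the apparent benefit is b = r × m.
- p = 0.5: m = 0.798, so b = 0.08, 0.16, 0.24 SD for r = 0.1, 0.2, 0.3.
- p = 0.7: m = 0.497, so b = 0.05, 0.10, 0.15 SD.

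With SE = √(v/(40p) + 1/40) and v = 1 − r²m(m − c), the two-sided rejection rate at a nominal 5% is Φ(b/SE − 1.96) + Φ(−b/SE − 1.96). Over r = 0.1 to 0.3 this is 6.0% to 14.5% for p = 0.5, and 5.5% to 9.4% for p = 0.7. Both r and p are assumptions; the documents give neither.

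**The case against.** **Completers may simply mean mothers with outcome data.** The sentence follows directly on the likelihood method, and questionnaires are sought whether or not the program is completed, so this meaning is available in both arms. That stands. A reader might infer that the plan compares selected BEAM mothers with unselected controls, but section {20c} never says program completers, and the BEAM rule applied literally would leave no controls at all. What remains is an undefined term whose only nearby definition is one-sided. The heading of {20c} refers to protocol non-adherence and Table 3 speaks of program completers, so the program reading is not far-fetched. The MoodMission questionnaire at T2 carries no completion threshold.

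**A definition may sit in the full protocol or analysis plan.** It may, and the missing definition alone would be a small matter. That does not remove the contradiction inside Table 3 or its mismatch with the precision statement.

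**Non-response is reported elsewhere.** A reader might infer that the questionnaire indicator hides non-response. At T3 it does not: retention has its own 80% criterion, and 70% retention would be classed as revise there. Nor do both denominators drop mothers with missing data, since a program completer who skips T3 stays in the first one. The gap is at T2.

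**The bias figures are modest and rest on a model.** This is fair. The main model tests time-by-group interactions, so only a correlation of participation with change matters. Every figure is below one standard error of the contrast: √(1/20 + 1/40) = 0.27 SD for 20 against 40, and √(1/28 + 1/40) = 0.25 SD for 28 against 40.

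**The plan never claims to probe departures from missing at random.** This is true. A complete-case re-run is nevertheless a weak check, because it generally needs stronger missingness assumptions than the analysis it is meant to support.

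**Conclusion.** The questionnaire-completion row contradicts itself, and the quoted precision belongs to a third denominator: ±12.4% should read ±13.9% to ±14.8% on the row's own criterion, with 20% to 30% lost from the BEAM arm. The change in precision is small. The larger problem is that a success-or-revise verdict can turn on the denominator, as in the 95% versus 79.5% example, which assumes 95% item completion. About 64% of T3 data could be present with both T3 indicators at their limits.

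The completers-only re-run is a poor sensitivity analysis on either reading: not applicable alike in both arms if based on program completion, and uninformative about missing at random if based on outcome data. The 0.05–0.24 SD distortion applies only if one arm is filtered and under the assumed correlations and completion rates. A reader might infer that the main treatment estimate is compromised. It is not, because it comes from the intent-to-treat likelihood analysis.

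**What to change.** 1. **One denominator for questionnaire completion.** Preferably use the share of expected items present among all randomised mothers, by arm and timepoint, against the same 80%. This also supplies the missing T2 figure. The cost is a less favourable number that overlaps with retention. The alternative is to keep follow-up responders in both the indicator and the criterion, restate the precision (±13.9% at 32, ±14.8% at 28), and add a T2 response rate.
2. **One definition of completer.** Define it identically in both arms by T2/T3 outcome data. Label any analysis by BEAM participation as descriptive and keep it out of the between-arm comparison.
3. **A real missing-data check.** Add a delta-adjusted analysis that shifts missing T2 and T3 PHQ-9 and GAD-7 values over a range stated in advance, and report where the conclusion changes.

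None of this needs new data. It takes a few sentences and a modest extra analysis. Collection of the primary outcomes was due to end in December 2022 and the analysts are not blinded, so the date on which these definitions are fixed should be recorded.
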